### Statistical analysis

We will adjust for all baseline covariates to estimate the initiator effect as hazard ratios, differences of cumulative incidence (risk) at 24 month, and risk curves using a marginal structural Cox proportional hazard regression model (MSM) with inverse probability of treatment weighting.[71,72]. For the per-protocol analysis, additional time varying confounding will be adjusted via censoring weights to mitigate selection bias from artificial censoring due to receipt of dose below key benchmark, treatment switching, violation of eligibility criteria including initiating pregnancy, incarceration, or treatment taper. However in the ‘clone-censor-weight’ approach for the sub-population (ix) and (x), we will not artificially censor for the violation of dosing benchmark and will estimate the artificial censoring weights conditional on their covariate history. Sandwich variance estimates will be used to compute the 95% compatibility (confidence) intervals for the adjusted hazard ratios,[73] while 500 bootstrap samples (with replacement) would be used to compute the compatibility intervals for risk differences and compatibility curves for risk curves.[74] We will apply high-dimensional propensity score (hdPS) and instrumental variable (IV) approaches for the initiator analysis as sensitivity analyses.[75,76] While the MSM and ‘clone-censor-weight’ approaches will target the marginal treatment effect, the IV analysis will estimate a local average treatment effect among compliers, i.e., individuals who would be prescribed the treatment preferred by treating physician or facility (see details in IV estimation section later). We will use SAS version 9.4 to prepare analytic data and conduct the statistical analysis using the SAS and R version 4.5.0.

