where $SW_{it}$ is the stabilized weight for the *i*th individual at time t, $C_{ij}$ is the censoring status for the *i*th individual at *j*th time, ${\bar{C}}_{ij}$ is the censoring history for the *i*th individual at *j*th time, $L_{i0}$ is the list of time-fixed covariates including treatment arm, ${\bar{L}}_{ij}$ is the time-dependent covariate history for the *i*th individual at *j*th time. Time-dependent covariates will be lagged by one week to ensure censoring is predicted using prior-week covariates. Same set of baseline and time-varying covariates will be included in the treatment and censoring models. Both treatment weights at time zero and censoring weights will be stabilized, truncated at the 99th percentile to limit the influence of extreme values and their product will be used as the final weights.[72] Covariate balance will be assessed using standardized mean differences (SMD), with SMD <0.10 considered balanced.[77] To fit the marginal structural model, a pooled weighted logistic regression model will be fitted to compare the time to OAT discontinuation, all-cause mortality, and overdose-related acute care visits across treatment groups. Based on the fitted models, individual time-to-event (survival) probabilities will be predicted weekly for each treatment arm by setting the treatment equal to a specific value (e.g., SROM, methadone, or buprenorphine/naloxone) for all individuals. These predicted probabilities will then be averaged across the population to get week-specific survival probabilities. The risk of the events will be estimated as one minus the averaged survival probability, with risk differences calculated for SROM initiators versus buprenorphine/naloxone and methadone. We will report hazard ratios, risk differences, and risk curves. Compatibility intervals and curves will be computed using the approach described in the Statistical analysis section.

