### hdPS estimation

As a sensitivity analysis, the treatment weights in the initiator analysis will be estimated using hdPS approach, an alternative to propensity score weighting, to address potential residual confounding, particularly for unmeasured differences in the severity of OUD and medical comorbidities among treatment groups. This semi-automated, data-driven method will identify proxy variables from administrative data for inclusion in propensity score models.[75] We will extract covariates from five data sources: DAD diagnostic codes (ICD-10, 4 digits), DAD procedure codes (5 digits), MSP diagnostic codes (ICD-9, 3 digits), MSP fee codes (5 digits), and PharmaNet drug therapeutic class 5 code (8 digits). Proxy variables will be assessed within a six-month window before time zero with exclusions for variables related to investigator-selected covariates, exposure, outcomes, colliders, and known instruments. Proxy covariates appearing in <50 individuals will be excluded to avoid concerns of positivity violations. To refine selection, three recurrence variables will be created for each candidate proxy (any occurrence, frequent occurrence above the median, and frequent occurrence above the 75th percentile), with duplicates removed. A Cox-LASSO regression will rank and select the top 200 covariates per outcome.[78] The selected empirical covariates, combined with investigator-selected covariates, will be incorporated into propensity score models estimated using multinomial logistic regression models or penalized regression methods such as LASSO to estimate the treatment weights.[79] In the marginal structural model, we will apply pooled weighted logistic regression using the final weights—calculated as the product of hdPS weights and censoring weights from the initiator analysis—to estimate hazard ratios, risk differences, and risk curves. Compatibility intervals and curves will be computed using the approach described earlier.

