### IV estimation

We will apply IV estimation for initiator analysis as a sensitivity method to address potential uncontrolled confounding. Given the lack of established IV methods for multi-category exposures in time-to-event analyses, we will define a binary exposure: SROM versus either methadone or buprenorphine/naloxone. Two candidate IVs will be tested: (a) prescriber-level preference for SROM and (b) facility-level preference for SROM, both measured among OAT clients in the six months prior to time zero.[80] The validity of the IV relies on four key assumptions. First, the relevance assumption will be tested using a logistic regression model to assess the association between the IVs and the exposure while adjusting for individual- and prescriber-level characteristics. The exclusion restriction and exchangeability cannot be directly verified, so their plausibility will be assessed through expert clinical input from our scientific advisory committee. Additionally, we will evaluate bias due to omitted measured covariates by comparing non-IV and IV analyses.[81] The assumption of homogeneity defines whether the IV-exposure association remains consistent across measured confounders of the exposure-outcome association.[82] The monotonicity assumption requires that there are no “defiers”, i.e., individuals who would always receive opposite treatment to that assigned by IV, and is expected to hold trivially in this context since OAT initiation with SROM is largely determined by prescriber or facility preference rather than individual choice. Since homogeneity and monotonicity cannot be empirically tested, their validity will be assessed through expert consultation.[80,83] To estimate the local average treatment effect, we will apply a two-stage residual inclusion (2SRI) approach.[84,85] In the first stage, a logistic regression approach will model the exposure as a function of the IV and selected covariates, generating residuals that account for uncontrolled confounding. These residuals will be incorporated into a Cox-PH model alongside the exposure and selected covariates. From this fitted model, we will estimate hazard ratios, risk differences, and risk curves. Compatibility intervals and curves will be computed using the approach described earlier.

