### Per-protocol analysis

We will conduct a per-protocol analysis to estimate treatment effects under sustained adherence at key dosing benchmarks, complementing the initiator effect.[86] To control the selection bias due to artificial censoring, we will consider two censoring models along with the propensity score models: (i) accounting for treatment switching, receipt of dose below key benchmark, and (ii) accounting for death, loss to follow-up, protocol violation by initiating pregnancy, dose taper, incarceration, or receipt of cancer or palliative care (see Table 3 for outcome specific censoring mechanism). Dose tapering is defined as two consecutive daily dose reductions without an intervening increase. Both censoring weights will be estimated using the approach described in the Initiator analysis section earlier. Final weights will be the product of the stabilized inverse probability of treatment weights at time zero and the post-baseline inverse probability of censoring weights, truncated at the 99th percentile. In the marginal structural model, we will apply a pooled logistic regression approach incorporating the final weights. The fitted model will be used to compute hazard ratios, risk differences, and risk curves. Compatibility intervals and curves will be computed using the approach described earlier. For sub-populations (ix) and (x), the censor-weighting approach will be similar, but we will apply a modified censoring mechanism as described in Table 3.

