### Subgroup and sensitivity analyses

We will conduct a range of sensitivity analyses by restricting the study population and timeline to pre-COVID era, redefining key variables, and applying alternative estimation methods including hdPS estimation, IV estimation (see Table 5 for details).

Because fentanyl had already become the dominant opioid in the drug supply by 2017, it will not be feasible to examinae the effect of pre-fentanyl era on our findings. Relevant findings from each analytical approach will be presented in a forest plot. Any deviations from this protocol will be documented in the final reports.

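### Hazard ratios are promised from a Cox model but taken from pooled logistic models with no rare-event condition; for OAT discontinuation the reported ratio may lie somewhat too far from 1

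*Protocol article*

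**What the plan says.** The protocol article describes the outcome model in several places.

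- **Statistical analysis:** the initiator effect is to be estimated as hazard ratios, risk differences at 24 months and risk curves, "using a marginal structural Cox proportional hazard regression model (MSM) with inverse probability of treatment weighting".
- **Initiator analysis:** "To fit the marginal structural model, a pooled weighted logistic regression model will be fitted to compare the time to OAT discontinuation", and likewise for the other two outcomes. Survival probabilities are predicted weekly from this model and averaged to give risks. The section then says: "We will report hazard ratios, risk differences, and risk curves".
- **hdPS estimation:** a pooled weighted logistic regression with different treatment weights is used "to estimate hazard ratios, risk differences, and risk curves".
- **Per-protocol analysis:** again a pooled logistic model. "The fitted model will be used to compute hazard ratios, risk differences, and risk curves".
- **IV estimation:** a Cox model with first-stage residuals. "These residuals will be incorporated into a Cox-PH model alongside the exposure and selected covariates".
- **Subgroup and sensitivity analyses:** "Relevant findings from each analytical approach will be presented in a forest plot".

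None of the three pooled-logistic sections states that the event must be rare per interval, plans a check of this, or names another link. Key measures makes OAT discontinuation a primary outcome for the initiator analysis and defines it as at least 5 days without dispensation for methadone and SROM, or at least 6 days for buprenorphine/naloxone.

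**The concern.** A pooled logistic model estimates the ratio of the odds of an event per interval. That ratio approximates the hazard ratio only when few of those at risk have the event in each interval. All-cause mortality would be expected to meet this condition on a weekly grid. Discontinuation is less certain, because a short dispensing gap counts as an event and stopping may be concentrated in the first weeks.

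Two things are at stake. First, the ratio reported for a primary outcome may be further from 1 than the hazard ratio it is labelled as. Second, the gap depends on baseline risk, and the study is designed to compare effects across ten sub-populations and to repeat the analysis with 14- and 30-day discontinuation definitions. If baseline discontinuation risk differs between these analyses, one and the same hazard ratio would be reported as different numbers.

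**Working it through.** The article states no weekly or cumulative discontinuation rate for this cohort, so there is no figure of its own to reproduce. The check asks how far the logistic ratio departs from the hazard ratio over a range of weekly risks.

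**Inputs**
- Interval: one week. The Initiator analysis section predicts weekly, and no other interval is given for the outcome model.
- Follow-up: at most 24 months, taken as 104 weeks.
- True hazard ratio (HR): 0.70 and 1.50, chosen for illustration.
- Weekly risk in the reference arm, p0: assumed, 2% to 30%. One further value comes from the only numeric retention rate in the article, 60.6% at 1 year in the cited German observational studies (Introduction). At a constant hazard this gives p0 = 1 − 0.606^(1/52) = 0.0096, or 0.96% per week. Those are other patients, and the article does not say how retention was defined there.

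**Formula.** Under proportional hazards:
- p1 = 1 − (1 − p0)^HR
- OR = [p1/(1 − p1)] / [p0/(1 − p0)]
- Excess on the log scale = ln(OR)/ln(HR) − 1

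**One case in full.** With p0 = 0.20 and HR = 1.50: 0.80^1.5 = 0.7155, so p1 = 0.2845. The odds are 0.2845/0.7155 = 0.3976 against 0.20/0.80 = 0.25. OR = 0.3976/0.25 = 1.590. The excess is ln(1.590)/ln(1.50) − 1 = 14%.

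**Constant weekly risk**

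| Weekly risk p0 | OR for HR 0.70 | OR for HR 1.50 | Log-scale excess (0.70 / 1.50) |
|---|---|---|---|
| 0.96% (from 60.6% at 1 year) | 0.699 | 1.504 | 0.4% / 0.6% |
| 2% | 0.698 | 1.508 | 0.9% / 1.3% |
| 5% | 0.695 | 1.520 | 2% / 3% |
| 10% | 0.689 | 1.541 | 4.5% / 7% |
| 15% | 0.683 | 1.564 | 7% / 10% |
| 20% | 0.676 | 1.590 | 10% / 14% |
| 30% | 0.662 | 1.651 | 16% / 24% |

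The last rows are demanding. If 20% of those still at risk stop every week, median retention is ln(0.5)/ln(0.80) = 3.1 weeks. At 30% it is 1.9 weeks.

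**Pooled over follow-up.** The planned model pools all weeks, so a high early risk is averaged with lower later risk. Week-saturated pooled models were fitted to expected counts over up to 104 weeks, with constant or front-loaded (Weibull, shape 0.7 and 0.5) hazards and assumed medians of 4 to 52 weeks.
- Logit link, all scenarios: 0.682 to 0.699 for a true 0.70, and 1.505 to 1.569 for a true 1.50.
- Logit link, front-loaded with a 4-week median (week-1 risk up to 29%): about 0.686 and 1.561, a log-scale excess of 6% to 10%.
- Complementary log-log link on the same records: 0.700 and 1.500 in every scenario.
- Fitted risk differences: within about 0.2 percentage points of the truth throughout.

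**Dependence on baseline risk.** A common hazard ratio of 1.50 would be reported as 1.508 where weekly risk is 2% and 1.590 where it is 20%.

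**The case against.** The strongest reply is that pooled logistic regression is a discrete-time way of fitting a marginal structural Cox model, that the Initiator analysis section presents it as such, and that a condensed article may leave interval and link to a fuller plan. This has force: the two sections are better read as a model and its approximation than as a flat contradiction. What stands is that the approximation carries a condition, and the article reports hazard ratios from it in three sections without stating that condition.

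Three stronger readings are tempting and are not supported.

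- *Discontinuation is too frequent here, so the primary effects are overstated.* The article gives no rate for this cohort. Its one retention figure implies a log-scale excess below 1% at constant hazard. That figure does not show that weekly risk is low here, but nothing in the article shows that it is high.
- *All primary results are affected.* Risks are computed as one minus the averaged predicted survival, so the odds ratio is never read as a hazard ratio in that step. Risk differences and curves are essentially unchanged, mortality should be little affected if rare per week, and a null effect stays null under either link.
- *Differences between the main, hdPS and IV estimates reflect the link.* Main and hdPS analyses use the same link. The IV analysis does use a Cox model, but it also has a binary exposure, targets a local effect among compliers and conditions on covariates, all of which the article discloses. A common link would remove one avoidable difference in the forest plot and would not make the estimates comparable.

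**Conclusion.** The point holds as a limited one. The article names a Cox model for its hazard ratios, takes them from pooled logistic models in the initiator, hdPS and per-protocol analyses, and states no rare-event condition. The direction of the error is certain: further from 1 whenever the hazard ratio is not 1. Its size is not known.

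For a true 1.50 on a weekly grid it runs from nothing visible at about 1% per week to 1.59 at 20%, with about 1.56 for a front-loaded pattern and a 4-week median. Every weekly risk other than 0.96% is an assumption, and the 0.96% is borrowed from other patients under a constant hazard. An excess of this order would rarely change a conclusion. The reason to act is that the error is avoidable, concerns a primary outcome, and varies with baseline risk across the sub-populations and discontinuation definitions that the study sets out to compare.

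**What to change.** In the Initiator analysis, hdPS estimation and Per-protocol analysis sections, obtain the hazard ratios in one of two ways and say which:

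1. the same pooled weekly model and weights, with a complementary log-log link in place of the logit; or
2. the weighted Cox model already named in the Statistical analysis section.

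Keep the risk curves and risk differences as planned. State the outcome-model interval (weekly) once, so that it applies to all three sections.

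The first option changes the link in the model statement and needs no new data or weights. The Study status and timeline section says no analyses have been conducted, so the change can be made before any result is seen.

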### hdPS estimation

As a sensitivity analysis, the treatment weights in the initiator analysis will be estimated using hdPS approach, an alternative to propensity score weighting, to address potential residual confounding, particularly for unmeasured differences in the severity of OUD and medical comorbidities among treatment groups. This semi-automated, data-driven method will identify proxy variables from administrative data for inclusion in propensity score models.[75] We will extract covariates from five data sources: DAD diagnostic codes (ICD-10, 4 digits), DAD procedure codes (5 digits), MSP diagnostic codes (ICD-9, 3 digits), MSP fee codes (5 digits), and PharmaNet drug therapeutic class 5 code (8 digits). Proxy variables will be assessed within a six-month window before time zero with exclusions for variables related to investigator-selected covariates, exposure, outcomes, colliders, and known instruments. Proxy covariates appearing in <50 individuals will be excluded to avoid concerns of positivity violations. To refine selection, three recurrence variables will be created for each candidate proxy (any occurrence, frequent occurrence above the median, and frequent occurrence above the 75th percentile), with duplicates removed. A Cox-LASSO regression will rank and select the top 200 covariates per outcome.[78] The selected empirical covariates, combined with investigator-selected covariates, will be incorporated into propensity score models estimated using multinomial logistic regression models or penalized regression methods such as LASSO to estimate the treatment weights.[79] In the marginal structural model, we will apply pooled weighted logistic regression using the final weights—calculated as the product of hdPS weights and censoring weights from the initiator analysis—to estimate hazard ratios, risk differences, and risk curves. Compatibility intervals and curves will be computed using the approach described earlier.

### IV estimation

We will apply IV estimation for initiator analysis as a sensitivity method to address potential uncontrolled confounding. Given the lack of established IV methods for multi-category exposures in time-to-event analyses, we will define a binary exposure: SROM versus either methadone or buprenorphine/naloxone. Two candidate IVs will be tested: (a) prescriber-level preference for SROM and (b) facility-level preference for SROM, both measured among OAT clients in the six months prior to time zero.[80] The validity of the IV relies on four key assumptions. First, the relevance assumption will be tested using a logistic regression model to assess the association between the IVs and the exposure while adjusting for individual- and prescriber-level characteristics. The exclusion restriction and exchangeability cannot be directly verified, so their plausibility will be assessed through expert clinical input from our scientific advisory committee. Additionally, we will evaluate bias due to omitted measured covariates by comparing non-IV and IV analyses.[81] The assumption of homogeneity defines whether the IV-exposure association remains consistent across measured confounders of the exposure-outcome association.[82] The monotonicity assumption requires that there are no “defiers”, i.e., individuals who would always receive opposite treatment to that assigned by IV, and is expected to hold trivially in this context since OAT initiation with SROM is largely determined by prescriber or facility preference rather than individual choice. Since homogeneity and monotonicity cannot be empirically tested, their validity will be assessed through expert consultation.[80,83] To estimate the local average treatment effect, we will apply a two-stage residual inclusion (2SRI) approach.[84,85] In the first stage, a logistic regression approach will model the exposure as a function of the IV and selected covariates, generating residuals that account for uncontrolled confounding. These residuals will be incorporated into a Cox-PH model alongside the exposure and selected covariates. From this fitted model, we will estimate hazard ratios, risk differences, and risk curves. Compatibility intervals and curves will be computed using the approach described earlier.

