## Introduction

### Slow-release oral morphine as an alternative OAT

Methadone and buprenorphine/naloxone are common pharmacological treatments for opioid use disorder (OUD) aimed at reducing unregulated opioid use, overdose risk, and associated harms.[1–10] However, not all individuals respond well to these treatments, necessitating alternative options such as slow-release oral morphine (SROM), extended-release naltrexone, extended-release buprenorphine, and injectable opioid agonist therapies.[6,8,11] Methadone, a full mu-opioid receptor agonist, has long been the gold standard for OAT due to its high retention rates but requires careful dose titration due to its long half-life, overdose risk, and potential for QT (a measure of the heart’s electrical cycle on electrocardiogram) prolongation.[12] Buprenorphine/naloxone, a partial agonist, has a better safety profile but exhibits a ceiling effect on opioid receptor activation, which may limit its efficacy for individuals with high opioid tolerance.[6]

In contrast, SROM is a full agonist with a long-acting formulation which provides stable plasma levels with once-daily dosing without a ceiling on its opioid effects, making it a potential alternative to methadone and buprenorphine/naloxone. Additionally, unlike methadone, SROM does not prolong the QT interval and may have a lower risk of sedation.[13–15] Originally developed for pain management, SROM has gained recognition as an opioid agonist treatment (OAT) in several countries, including Austria, Germany, and Canada, though its regulatory approval status varies. SROM, marketed as Kadian^®^, a 24-hour extended-release morphine capsule, was introduced in 2017 under British Columbia, Canada’s (BC) provincial drug plan (PharmaCare) as an off-label option for individuals who have not found success with methadone or buprenorphine/naloxone, though it is unclear who are most likely to benefit.[5,6]

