Alternative treatment weights using hdPS	Alternative specification of propensity score models to reduce residual confounding (see hdPS estimation section)	Initiator
IV estimation	Prescribing preference-based IV will be applied to reduce residual confounding (see IV estimation section).	Initiator

BC, British Columbia; IPTW, inverse probability of treatment weighting estimation; hdPS, high dimensional propensity score estimation; IV, instrumental variable estimation; ED, emergency department; OAT, opioid agonist treatment; OUD, opioid use disorder;

c. Restricted to the lower mainland Vancouver area (declaration of public health emergency);

d. number of treatment interruptions prior to time zero;

e. binary exposure (which are the same as constructed for IV analysis): 1 for specific dose adjustment strategy, and 0 for no dose change group.

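### The IV sensitivity analysis pools methadone and buprenorphine/naloxone, so its hazard ratio can partly reflect comparator mix, and no non-IV estimate with the same comparator is specified

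*Protocol article*

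**What the plan says.** The main initiator analysis keeps three arms. A multinomial model gives the treatment weights, and the results are "risk differences calculated for SROM initiators versus buprenorphine/naloxone and methadone" (Initiator analysis section).

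The IV section departs from this. "Given the lack of established IV methods for multi-category exposures in time-to-event analyses", it uses a two-group exposure: "we will define a binary exposure: SROM versus either methadone or buprenorphine/naloxone". There are two candidate instruments, "a) prescriber-level preference for SROM and (b) facility-level preference for SROM, both measured among OAT clients in the six months prior to time zero". Estimation is by two-stage residual inclusion (2SRI). First, "a logistic regression approach will model the exposure as a function of the IV and selected covariates". Then, "These residuals will be incorporated into a Cox-PH model alongside the exposure and selected covariates".

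The exclusion restriction is left to advisory-committee judgement, and the comparator mix is not mentioned. The Statistical analysis section describes the result as a local effect among compliers. Table 5 gives the purpose: "Prescribing preference-based IV will be applied to reduce residual confounding". The Subgroup and sensitivity analyses section places results from each approach in a forest plot.

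The prescriber-related items in Table 4 are attachment, payment plan and practice size. None describes how a prescriber divides non-SROM clients between the two comparators.

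**The concern.** The instrument should move the outcome only through SROM versus not-SROM. With three drugs collapsed into two groups, the reference group is itself a mixture. If prescribers who favour SROM also use relatively more (or less) methadone for their other clients, the instrument changes that mixture too, and the 2SRI model attributes any resulting outcome difference to SROM.

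The protocol gives grounds to take this seriously. It describes SROM and methadone as full agonists and buprenorphine/naloxone as a partial agonist, so preferences for the drugs may be linked. It also expects the comparators to differ: methadone "has long been the gold standard for OAT due to its high retention rates", and the cited French cohort gives different overdose and mortality ratios for the two.

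At stake is how the IV row in the forest plot is read. It could disagree with the main result, or agree with it, for reasons unrelated to unmeasured confounding.

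**Working it through.** The protocol gives no sample size, event count or comparator mix for this analysis, so there is no figure to reproduce.

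**Step 1: mechanism on a linear scale.** At preference level z, let s_z be the SROM share, m_z the methadone share among non-SROM clients, and μ the mean outcome on each drug (S, M, B). Then

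E_z = s_z·μ_S + (1 − s_z)·[m_z·μ_M + (1 − m_z)·μ_B].

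Let SROM equal a fixed mix m* of the comparators, so the true effect is zero, and write δ = μ_M − μ_B. The IV ratio between levels 1 and 0 is then

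(E_1 − E_0)/(s_1 − s_0) = δ·[(1 − s_1)(m_1 − m*) − (1 − s_0)(m_0 − m*)]/(s_1 − s_0).

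This is zero if δ = 0, or if m_1 = m_0 = m*. A leak therefore needs both a shifting mix and differing comparators. A small SROM difference in the denominator magnifies it.

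**Step 2: do the comparators differ?** From the French cohort figures in the Introduction, the implied crude methadone:buprenorphine ratios are 3.8/2 = 1.90 for overdose and 9.1/3.9 = 2.33 for mortality. They are unadjusted, and the protocol itself notes potential selection bias there.

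**Step 3: simulation of the planned 2SRI.** All settings are assumptions: 9,000 initiators, 300 prescribers, 24 months, one unmeasured confounder, and SROM exactly equal to a 50:50 mixture of the comparators. The first stage is logistic; the raw residual enters a Cox model with a prescriber-clustered sandwich SE. There were 300 replicates per cell (Monte Carlo SE at 5%: √(0.05 × 0.95/300) = 1.3 points).

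Methadone share = 0.5 + b·q + N(0, 0.10), with q the standardised SROM preference. The correlation is b/√(b² + 0.10²): 0.45 for b = 0.05 and 0.71 for b = 0.10. These correspond to 14- and 28-point differences in methadone share between the top and bottom quintiles of preference.

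Cells show mean IV HR, then the percentage of 95% intervals excluding 1. Adjusted means that the methadone share is added to both stages.

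| Outcome, methadone:buprenorphine HR | 14-point shift | Adjusted | 28-point shift | Adjusted |
|---|---|---|---|---|
| Discontinuation-like, 1.0 | 1.00, 6% | – | 1.00, 6% | – |
| Discontinuation-like, 0.8 | 0.94, 10% | 1.01, 6% | 0.88, 26% | 1.03, 8% |
| Discontinuation-like, 0.6 | 0.87, 30% | 1.03, 6% | 0.75, 78% | 1.07, 9% |
| Mortality-like, 1.5 | 1.11, 10% | 0.96, 7% | 1.24, 12% | 0.92, 6% |
| Mortality-like, 1.9 | 1.17, 11% | 0.95, 8% | 1.39, 23% | 0.89, 7% |
| Mortality-like, 2.33 | 1.23, 16% | 0.93, 6% | 1.54, 32% | 0.87, 8% |

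With no shift, HRs were 0.98-1.00 and exclusion 4-6%. The adjusted runs used each prescriber's true mix, so they are optimistic.

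**Step 4: weaker associations.** A similar simulation (200 replicates) used buprenorphine:methadone HRs of 1.25 and 1.6. Exclusion was 7% and 8% at correlation 0.18, 9% and 15% at 0.30, and 17% and 46% at 0.53, against 6% with no leak. The Monte Carlo SE near 7% is 1.8 points, so correlation 0.18 is not distinguishable from no leak.

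**Step 5: SROM simply displaces one comparator.** If SROM replaces only methadone, (1 − s)m = a − s with the buprenorphine part fixed, and the Step 1 ratio becomes exactly μ_S − μ_M. With buprenorphine:methadone HR 1.6 and SROM a 50:50 mixture, the initial HR is (1 + 1.6)/2 = 1.30 against methadone and 1.30/1.6 = 0.81 against buprenorphine. Simulation (120 replicates) gave:

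- 1.25 (38% excluding 1) when only methadone is displaced;
- 0.84 (20%) when only buprenorphine is displaced;
- 0.99 (3%) under proportional displacement.

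In the methadone case, adjusting for the share cut exclusion to 21% but left the HR at 1.25, so adjustment did not move the estimate.

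**Step 6: like-for-like comparison.** The Initiator analysis section specifies SROM versus each drug; the IV section specifies SROM versus the two pooled. No weighted model with the pooled exposure is specified.

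**The case against.** Several stronger readings are tempting and do not hold.

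- A reader might infer that pooling breaks the exclusion restriction by construction. It does not: Steps 1 and 3 show nominal behaviour when either condition is absent, and the protocol is silent on how the mix varies with SROM preference.
- A reader might treat the percentages above as type I error of a stated test. The protocol states no null hypothesis or test for this analysis, only 95% compatibility intervals; the percentages describe how often such an interval would exclude 1.
- A reader might call the IV analysis the plan's chief defence against unmeasured confounding. It is one sensitivity analysis, for the initiator effect only, and the Discussion names the high-dimensional propensity score as the mitigation.

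Pooling is also disclosed and given a reason, which is accepted here. The IV section mentions prescriber-level characteristics and selected covariates without listing them, and Table 4 is headed for the weighting models. The mix could therefore be included in a fuller document; nothing shown says so.

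The IV section does plan to compare IV with non-IV analyses, which may suggest a common binary exposure. That sentence concerns bias from omitted measured covariates, however, and specifies no pooled effect estimate.

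Finally, under pure displacement the IV result can be defended as a valid complier effect against the displaced drug. That stands. But the plan labels the contrast as SROM versus either drug and has no step to show which drug was displaced.

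**Conclusion.** The point holds as a conditional risk. The pooled IV hazard ratio absorbs part of the methadone-versus-buprenorphine difference if the comparator mix tracks SROM preference and the two drugs differ in outcome. The effect is small when the association is weak (correlation about 0.2) and can be material when it is strong: with no SROM effect, mean HRs ran from 0.75 to 1.54 at correlations of about 0.45-0.71. These sizes, and the direction, depend on assumed associations, comparator HRs and cohort size.

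The comparator mismatch needs no simulation. As specified, IV and non-IV rows in the forest plot would refer to different contrasts. The main three-arm analysis is unaffected.

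**What to change.** 1. Fit the weighted initiator model once with the same pooled binary exposure, and show it beside the IV result in the forest plot.
2. For each prescriber or facility, compute the methadone share among non-SROM clients over the same six months, and report it by level of the SROM-preference instrument.
3. Repeat the 2SRI with that share as a covariate in both stages. State that this removes the leak only where the mix varies partly independently of SROM preference (Step 5).
4. State the comparator mix to which the IV estimate refers, and limit its interpretation if the mix varies with the instrument.

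**Cost.** One further variable from PharmaNet, already linked, one extra weighted model and one repeat of the 2SRI. The IV interval widens: in a simulation with buprenorphine:methadone HR 1.6, the SD of the log HR rose from about 0.14 to 0.17-0.19, or 21-36% (0.17/0.14 = 1.21; 0.19/0.14 = 1.36).

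The share will be noisy in small practices. Table 4 defines these as at most 15 clients in 12 months. Even with all 15 counted, the sampling SE of a 50% share is √(0.25/15) = 0.13, about as large as the 0.10-0.12 SD assumed above for variation in the share unrelated to SROM preference.
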